A recent review shows that adherence to CBTI in the clinical settings ranges from 32–52% [21]. The lowest rates were in clinical effectiveness studies and studies with comorbid populations [21]. Not surprisingly, even modest improvements in CBTI adherence can improve outcomes [22]. Findings from a study of 696 clients with insomnia found that those who completed treatment with high adherence improved significantly more than completers with low adherence [22]. Additionally, adherence is the strongest predictor of long-term (e.g. 1 year) outcomes [22]. Attrition also reduces the benefits of treatment, especially in clinical settings where dropout rates are reported to be as high as 39% [23, 24]. A study on the national dissemination of CBTI in the US Veteran Affairs Healthcare System reported that 33% of clients dropped out [24]. Together, these studies suggest a sizable proportion of clients are likely not to be fully benefiting from CBTI. Efforts to broadly implement CBTI would benefit from ways to improve treatment adherence and completion rates. There currently are no evidence-based recommendations for augmenting either treatment adherence or completion in CBTI.

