### Couples and sleep

The literature on couples and sleep is relatively sparse, especially in the context of insomnia. However, recent reviews and the few observational studies in this domain highlight several important points. Importantly, sleep is often a social experience since the majority of adults have bed partners [33]. Consistent with this idea, couples prefer to sleep in the same bed and report worse sleep when they sleep alone, despite objective evidence for negative consequences on sleep from co-sleeping [34]. Moreover, couples influence each other’s sleep. For example, Lee et al. found sleep duration covaried within couples on a daily basis, and sleep quality covaried within couples when averaged across several days [35]. Sleep is also related to relationship satisfaction. For example, Troxel et al. found sleep disturbance, including insomnia, and relationship satisfaction were associated [33]. Similarly, those with sleep-onset insomnia were more likely to report relationship problems as a result of their own or their partner’s sleep issues [36]. Another study found higher marital satisfaction was linked to higher sleep-wake concordance in couples [37], and a large study (*n* = 405 couples) found a spouse’s sleep problems predicted higher levels of marital unhappiness [38]. Finally, couple-level variables, including bed partner behaviours, can perpetuate insomnia [34]. For example, bed partners can encourage a client to sleep in or take a nap after a bad night of sleep, or to read, watch TV, etc. in bed until they become sleepy, or they can increase a client’s attentional preoccupation with sleep by asking about their sleep in the morning. While these behaviours are generally well-intended, they are all antithetical to treatment. Therefore, evidence suggests that partners affect each other’s sleep and relationship satisfaction, and thus incorporating a partner into CBTI has the potential to significantly impact outcomes. Surprisingly, though, no published studies report development or testing of a CBTI intervention incorporating the partner.

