#### Statistical tests of hypotheses

##### Aim 1

Hypothesis 1A predicts that individuals under partner-assisted conditions will show greater adherence and lower attrition than those under the individual treatment condition. We will test this with 3 × 5 (group × session) MANOVA. The MANOVA will first test the entire set of adherence variables by constructing a latent variable of adherence and using this as the outcome variable. If significant, we will then examine the univariate results for each specific adherence measure. Significant main effects of group (the hypothesised effect) will be followed by comparing PA-CBTI with each of the other groups. Hypothesis 1B will use the Chi-squared test to test the proportion of participants who complete each treatment, with similar follow-ups.

##### Aim 2

Hypothesis 2A anticipates that greater adherence will relate to better sleep outcomes in PA-CBTI and i-CBTI, but not PA-SMT. Multiple regressions will test the hypothesis, with explanatory variables of group (dummy coded), adherence (in the last week of treatment), and group × adherence interaction. The outcome variable will be diary-derived sleep efficiency in the last week of treatment. The interaction term is the effect of interest. Follow-ups will examine the adherence effect within each group. Hypothesis 2B will be tested with Sobel mediation. We hypothesise that PA-CBTI will show (via sleep diaries) greater mean daily sleep efficiency at post-treatment and 6-month follow-up compared with i-CBTI. This effect will be mediated by adherence at the end of treatment (adherence cannot be measured at follow-up since we will not be prescribing sleep schedules).

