### Limitations

A limitation of the current study is that neither clients nor clinicians are blinded to the treatment condition, a problem inherent to any intervention of psychotherapy. However, clients are blinded to the study hypotheses and staff who score polysomnography, actigraphy, and questionnaires are blind to treatment condition.

In addition, because we want to be reflective of a clinic-based population, and for the sake of feasibility and to reduce participant burden, the ‘baseline’ sleep diary and actigraphy data are collected between weeks 1–2 of treatment. Hence, this may not be considered as a true baseline. However, between weeks 1–2 the active intervention has not yet commenced as the first session consists of education only. Similarly, our ‘post-treatment’ sleep diary and actigraphy data are collected between weeks 6–7 of treatment. However, the final treatment session is a summary session only and no additional treatment strategies are introduced. All other post-treatment data (e.g. questionnaires) are collected after completion of treatment session 7.

We do not conduct a diagnostic assessment in the partners. Thus, it is possible some of them meet the criteria for a sleep disorder. While we considered conducting such screens, conceptually we do not believe the presence of a sleep disorder should have an impact on the partner’s ability to perform the role defined for them within the intervention. We do, however, have the STOP-Bang from screening, as well as Insomnia Severity Index, sleep diary, and actigraphy at each assessment time point. Thus, we can assess the risk of obstructive sleep apnoea and track symptoms of insomnia in the partners. If we have a couple where both partners report insomnia upon initial contact with the research team, we ask the couple to decide who will enrol as the “client” and who will enrol as the “partner.” While the partner is not required to adopt treatment recommendations themselves, they are welcome to change their behaviour in accordance with treatment if they so desire. This is true whether or not the partner reports sleep problems. Not having formal diagnostic information on the partners limits our ability to assess effectiveness of the interventions in couples where both individuals experience a diagnosed sleep disorder.

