### Strengths

Strengths of the current project include the range of outcome variables, which permits high-quality analysis. Our focus on optimising external validity by maximising generalisability to clinical settings and implementing relatively few exclusion criteria is a significant strength, given clinic-based studies and clients with comorbidities show reduced adherence and completion relative to more tightly controlled RCTs. In addition, our control condition, sleep management therapy (PA-SMT), is a valuable control given that it is considered ‘treatment as usual’ in the community. Results could lead to the dissemination of a new CBTI intervention that helps more people adhere to and complete treatment, ultimately benefiting a greater number of people who seek treatment for insomnia. PA-SMT allows us to assess for the unique contribution of the partner independent of the active treatment. Another strength of this trial is our multimodal assessment of sleep; that is, both prospective (e.g. sleep diaries) and retrospective (e.g. ISI) data are collected. Furthermore, we control for clinician time and effort in that clinicians dedicate the same amount of time and effort to each of the three treatment conditions. This trial is also not limited to the investigation of how the interventions impact on sleep since data on broader outcomes will be analysed, including relationship functioning and mental health. Finally, this trial will allow a robust analysis of the impact of insomnia and its treatment on the bed partner, something not examined to date (Additional file 1).

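### The Aim 2 models name no baseline covariate, so the within-arm adherence slopes (H2A) and the adherence-to-sleep path (H2B) are open to confounding by client comorbidity

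*Protocol article*

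**What the plan says.** The Aim 2 part of Statistical tests of hypotheses sets out the H2A model: "Multiple regressions will test the hypothesis, with explanatory variables of group (dummy coded), adherence (in the last week of treatment", and the product of group and adherence. The outcome is diary sleep efficiency in that same last week. It adds "The interaction term is the effect of interest" and "Follow-ups will examine the adherence effect within each group". For the other hypothesis, "Hypothesis 2B will be tested with Sobel mediation", with end-of-treatment adherence as the mediator. Neither analysis lists a baseline covariate.

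On comorbidity, the section on adherence and attrition says of clinic adherence that "The lowest rates were in clinical effectiveness studies and studies with comorbid populations". Strengths says that "clients with comorbidities show reduced adherence and completion relative to more tightly controlled RCTs", and counts the small number of exclusions as an advantage. The SCID-5 and a set of self-report measures belong to the pre-treatment visit (Screening and eligibility). The PHQ-9, PCL-5 and BAI are given at the major assessments, and randomisation follows the pre-treatment assessment (Study intervention).

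On the partner, Couples and sleep says that "evidence suggests that partners affect each other’s sleep and relationship satisfaction". Limitations says "conceptually we do not believe the presence of a sleep disorder should have an impact on the partner’s ability to perform the role defined for" the partner.

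**The concern.** Randomisation protects comparisons between arms. It does not protect a slope of sleep on adherence within an arm, or the second leg of a mediation model. A client with marked depression or anxiety may both follow the programme less closely and sleep less efficiently. A model without that factor credits the whole association to adherence.

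The article means to read these quantities causally. Aim 2 is framed as testing whether adherence bears directly on outcome, Hypothesis 2B attributes better sleep at follow-up to increased adherence, and the Publications section plans a main paper on the impact of adherence on insomnia symptoms. At stake is the trial's account of mechanism, not its randomised comparison of adherence.

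**Working it through.** The article gives no power, effect size or correlation for Aim 2, so there is no planned figure to reproduce. The check asks how far an omitted common cause could move the planned statistics if adherence had no effect on sleep.

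**Inputs**
- From Power considerations: three arms of 40.
- From the Aim 2 text: the H2A regressors, and a Sobel test, applied here to PA-CBTI against i-CBTI.
- Assumed: partner involvement (P = 1 in the partner-assisted arms) raises adherence by 0.5 SD; one baseline factor U lowers both adherence and sleep efficiency with standardised path c, for c from 0 to 0.5; the true adherence effect is 0.

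**Formulas**
- Adherence: A = 0.5·P − c·U + √(1 − c²)·e₁
- Sleep efficiency: S = −c·U + √(1 − c²)·e₂
- Within an arm, Var(A) = 1 and Cov(A, S) = c², so the spurious slope is c².
- Spurious indirect effect = a·b = 0.5·c².
- Sobel z = ab / √(a²·se_b² + b²·se_a²), rejecting when |z| > 1.96.

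**Results** (2000 simulated trials per row; the slope is that of the i-CBTI arm)

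| c | Slope bias, c² | Simulated bias | False-positive rate of slope | Indirect effect, 0.5·c² | Simulated | Sobel rejection, U omitted | Sobel rejection, U in both equations |
|---|---|---|---|---|---|---|---|
| 0 | 0 | 0.00 | 5.2% | 0 | 0.00 | 0.6% | 0.6% |
| 0.2 | 0.04 | 0.04 | 5.2% | 0.02 | 0.02 | 0.8% | 0.6% |
| 0.3 | 0.09 | 0.09 | 7.9% | 0.045 | 0.045 | 1.7% | 0.7% |
| 0.4 | 0.16 | 0.16 | 17.3% | 0.08 | 0.08 | 5.7% | 0.8% |
| 0.5 | 0.25 | 0.25 | 35.4% | 0.125 | 0.126 | 17.5% | 1.1% |

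Formula and simulation agree. With U in both equations the mean indirect effect returns to about 0.00 at every c.

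**The interaction test (H2A's effect of interest)**
- If U acts equally in all arms, the 2-df test rejects in 4.9% to 5.4% of trials across the range. A bias common to every slope cancels in the comparison of slopes.
- If U affects adherence only in the two CBTI arms, rejection is 6.0%, 10.3% and 19.4% for c = 0.3, 0.4 and 0.5.

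Simulation error is about √(0.05 × 0.95 / 2000) = 0.5 percentage points near 5%. The adjusted column uses U itself. A questionnaire measures comorbidity with error and would remove only part of the bias.

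**The case against.** The case on the other side has several parts.

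- **The text supplies only one leg.** It links comorbidity to lower adherence, and does so largely by comparing studies and settings. It does not say that comorbidity lowers sleep efficiency among treated clients, and the background notes benefit in both primary and comorbid insomnia. This stands: the second leg is an assumption, and the most that can be said is that the paths are open to confounding.
- **H2A is worded as an association, and its target is the interaction.** This stands in part. PA-SMT, where sleep restriction and stimulus control adherence is also calculated, protects the interaction if confounding is similar across arms. It does not protect the within-arm follow-ups or H2B.
- **Sobel is conservative.** Rejection passes 5% only at paths of about 0.4 or more. This stands for the test, but the estimated indirect effect is biased at every non-zero path.
- **Covariates may be set in a document not shown.** This is reasonable for H2B, where only the method is named. It is weak for H2A, where the regressors are listed.

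A reader might go further and infer that the partner's own sleep problem is a second documented common cause. The article supports an influence on the client's sleep, but nowhere an influence on the client's adherence, and the belief stated in Limitations points the other way. How partners affect each other's sleep is also listed among the possible exploratory analyses. A reader might also extend the point to Hypotheses 1A and 1B. Those are randomised comparisons, where leaving out covariates affects precision only and does not confound.

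**Conclusion.** The point holds for the H2A within-arm adherence slopes and for the adherence-to-sleep path of H2B. The sizes found rest on assumed paths of 0.2 to 0.5 to both variables, a 0.5 SD partner effect on adherence, and 40 clients per arm. At 0.2 the consequence is negligible for testing; at 0.4 to 0.5 a within-arm slope is falsely significant in about one trial in six to one in three. The documents do not show that confounding is present or how strong it is, and the planned interaction test is affected only if the confounding differs by arm. Aim 2 is secondary, but it carries the causal claim about adherence, and the remedy uses data the trial already plans to collect.

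**What to change.** In the Aim 2 text, add two pre-randomisation client covariates to the H2A regression and to both H2B equations (adherence on group, and sleep efficiency on group and adherence): the PHQ-9, or a SCID-5 comorbidity indicator, and the ISI. Confirm the timing of both questionnaires against the assessment schedule in Table 2. The baseline diary should not stand in for them as a pre-randomisation covariate, because Limitations places it between weeks 1 and 2 of treatment.

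Baseline partner ISI may be added as an optional predictor of the client's sleep, without calling it a documented common cause. Say in the text that within-arm slopes and the mediated effect remain observational after adjustment.

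The cost is wording and a few degrees of freedom. With 120 clients the H2A model has six coefficients, so two covariates take the residual degrees of freedom from 114 to 112; each H2B equation also loses two. No new data are needed.

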#### Cognitive behavioural therapy for insomnia (CBTI) and partner-assisted CBTI (PA-CBTI)

We employ a CBTI protocol based on those recommended by the leading experts in the field [40, 41]. This protocol covers the four-factor model of insomnia, sleep restriction, stimulus control, sleep hygiene, stress and relaxation, cognitions and sleep, and relapse prevention. PA-CBTI follows the same session outline as CBTI. The “partner-assisted” aspect involves: (a) teaching the partner all of the same concepts and psychoeducation as provided to the client; (b) providing handouts of session material tailored specifically for the partner; (b) actively engaging the partner in all treatment-related decision making and problem-solving; and (d) actively engaging the partner in determining how they can assist the client to implement treatment recommendations at home and assigning those behaviours as the partner’s homework. For example, we engage the partner along with the client in reviewing sleep diaries of the client, identifying patterns, deciding on changes to make, and determining whether/how to titrate time-in-bed for the coming week. The partner also actively assists the client to pick bed/wake times, activities and locations related to stimulus control principles, and strategies for staying awake and/or avoiding naps, etc. In essence, anything a client does in traditional CBTI is done with input from the partner in PA-CBTI. The therapist emphasises empowerment of the partner to provide support and structure for the client at home to maximise adherence to the intervention.

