##### Sleep diaries

Sleep diaries are widely used in studies of insomnia [44]. Each morning, participants are asked to record sleep habits such as bedtime, wake time, time in bed, and number and duration of awakenings and naps. Weekly averages are calculated. Sleep diaries include questions to track treatment adherence. Adherence to sleep restriction is calculated as average nightly deviation, in minutes, between the prescribed bed/wake times and reported times, plus any nap time [41, 45]. Note that, consistent with sleep restriction, clients are not considered “non-adherent” if they go to bed later or wake up and get out of bed earlier than scheduled times as they are taught this will simply increase sleep debt and aid treatment. Stimulus control adherence involves two questions: the first asking how many wake minutes after lights-out were spent out of bed (we then calculate that as a proportion of total wake minutes), and the second asking how many minutes outside the sleep window were spent in bed doing any activity other than sleep. Sleep management therapy adherence is measured by documenting the extent to which the treatment recommendation(s) to be practised each week is followed. Additionally, adherence to sleep restriction and stimulus control will still be calculated, despite these not being treatment recommendations. Hence, this group serves as a control for how much these behaviours change without a specific focus on them. While having several measures of adherence poses analytical challenges, the advantage is it allows us to assess exactly where, if anywhere, adherence fails. Adherence measures are obtained in sessions 3–7 (changes to sleep commence at session 2). We considered also using actigraphy to assess adherence (i.e. objective measure of bed time/wake time in sleep restriction). However, we decided against this, since actigraphy cannot measure stimulus control (i.e. cannot determine whether motion is in or out of bed) or assess sleep hygiene.

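### Aim 2 cannot by itself separate adherence improving sleep from earlier sleep improving the adherence score, because part of that score is set against a window reviewed weekly from the client's diaries

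*Protocol article*

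**What the plan says.** **Models (Statistical tests of hypotheses, Aim 2).** For 2A the regressors are "explanatory variables of group (dummy coded), adherence (in the last week of treatment), and group × adherence interaction". The response is sleep efficiency taken from the diaries of that same week. The interaction is named as the effect of interest, and the slopes within each group are follow-ups. For 2B, PA-CBTI is expected to show "greater mean daily sleep efficiency at post-treatment and 6-month follow-up compared with i-CBTI", tested by Sobel mediation: "This effect will be mediated by adherence at the end of treatment".

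**Timing (Limitations).** The post-treatment "sleep diary and actigraphy data are collected between weeks 6–7 of treatment", so the 2A predictor and outcome, and the post-treatment part of 2B, come from the same diary period.

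**Scoring (Sleep diaries).** "Adherence to sleep restriction is calculated as average nightly deviation, in minutes, between the prescribed bed/wake times and reported times, plus any nap time". Clients lose nothing "if they go to bed later or wake up and get out of bed earlier than scheduled times". One stimulus-control item counts non-sleep minutes in bed outside the window. The other is the share of wake minutes spent out of bed. The clinician-rated form (Client adherence form) is a 1 to 6 rating. The article does not say which of these enters Aim 2.

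**Window (section on CBTI and PA-CBTI).** The client's diaries are reviewed, which leads to "deciding on changes to make, and determining whether/how to titrate time-in-bed for the coming week". PA-CBTI uses the same session outline as individual CBTI, so this applies to both arms.

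**Interpretation.** Hypothesis 2A is worded as an association. Aim 2 speaks of the impact of adherence, and Hypothesis 2B attributes better 6-month sleep to it.

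**The concern.** The adherence score depends on the target as well as on behaviour. If the target is set or revised from how the client has been sleeping, a client who improves for any reason may be scored against a wider window, and the same habits then earn a better score. Earlier sleep also predicts later sleep. It therefore becomes a common cause of last-week adherence and of the sleep outcome, and the listed covariates do not block that path.

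This is separate from any minutes shared between a diary-based score and a diary-based outcome. It would persist with another sleep instrument. It also persists at 6 months, where the mediator does precede the outcome; there the problem is confounding by earlier response, not simultaneity.

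At stake is the conclusion of Aim 2. A positive result could be published as evidence that adherence improves sleep when it partly reflects responders being scored against an easier target.

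**Working it through.** The plan states no power or effect size for Aim 2 (its 0.81 is for Hypothesis 1A), so there is no figure to reproduce. The article also gives no titration rule, means or SDs. All simulation inputs below are assumptions that show possible size. They are not clinical proposals.

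**Step 1: direction of the score.** Deviation = max(time in bed − window, 0). Take an assumed habit of 500 min, a window of 380 min and a compliance fraction of 0.65. Time in bed is 380 + 0.35 × (500 − 380) = 422 min, so the deviation is 42 min. With the same 422 min and a window 15 min wider, it is 422 − 395 = 27 min. Because the score is one-sided, widening the window cannot worsen it for unchanged behaviour.

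**Step 2: within-arm slope, true effect zero.** One CBTI arm, 40 clients, five adherence weeks, 1000 runs, two-sided 5% test. Assumed inputs:
- baseline sleep efficiency 75 (SD 8), rising by 8 points regardless of adherence
- weekly noise SD 4, week-to-week correlation 0.5
- habitual time in bed 500 (SD 40) min
- compliance fraction uniform on 0.3 to 1, independent of sleep

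Last-week sleep efficiency is regressed on last-week adherence.

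| How the window is set | Mean r | Significant, unadjusted | Adjusted for previous week's sleep | Adjusted for all earlier weeks |
|---|---|---|---|---|
| Independent of sleep | −0.01 | 5.4% | 5.2% | 5.2% |
| Start independent, 15-min weekly shifts by sleep | 0.42 | 81.4% | 6.6% | 6.0% |
| Start independent, 30-min weekly shifts by sleep | 0.56 | 98.1% | 8.2% | 6.1% |
| Start from diary sleep, no shifts | 0.38 | 68.9% | 9.7% | 6.9% |
| Start from diary sleep, 15-min shifts | 0.56 | 97.7% | 11.8% | 6.8% |

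**Step 3: other inputs, and 6 months.** Inputs: baseline efficiency 70 (SD 8); improvement 12 (SD 6 or 3) unrelated to adherence; weekly noise SD 5; habitual time in bed 510 (SD 40) min; compliance Beta(3,2); first window equal to baseline sleep time or fixed at 360 min; shifts of 15 or 30 min. Slope rejection at 40 per arm:

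| Outcome | Unadjusted | Baseline sleep only | Window, baseline and preceding weeks |
|---|---|---|---|
| Last week | 38–82% | 13–29% | 5–7% |
| 6 months | 35–77% | 11–27% | 5–7% |

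**Step 4: the planned 2A test.** The within-arm slope is only a follow-up. The planned interaction test was significant in 18% to 37% of runs in settings where the slope was significant in 69% to 99%. Under other assumed inputs, and depending on how PA-SMT is scored, it ranged from 5% to 30%.

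**Step 5: the planned 2B test.** With no true arm difference in adherence, the Sobel test rejected in about 3% of runs or fewer (1.5% to 2.3% in one set). With a true difference, as Hypothesis 1A expects, and still no effect of adherence on sleep, it rejected in about 90%. That rate depends on the assumed difference. Sobel z = 1/√(1/z_a² + 1/z_b²), which is below the smaller of z_a and z_b, so the rate cannot exceed the power of the arm comparison on adherence. At 40 per arm, 90% needs a standardised difference of about (1.96 + 1.28) × √(2/40) = 0.72. At 0.5 the ceiling is about 61%.

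**Step 6: which measure is used.** When the window-scored deviation was averaged with three measures not linked to the window, slope rejection fell from 60–72% to about 10%. This is a favourable case, since one stimulus-control item does use the window.

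**Step 7: what adjustment costs.** With a true cumulative adherence effect and a fixed window (nothing to correct), adding preceding-week sleep efficiency cut the slope to 46–48% of its value. Power at 80 clients fell from 65% to 50% in one setting and from 94% to 78% in another. A further run gave about half the slope, and power fell from about 75% to 53%.

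**The case against.** The strongest reply has four parts.

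1. The article says only that the client, partner and therapist decide whether and how to change time in bed. A reader might infer that good sleep is documented to produce good adherence scores. It is not: no rule or direction is given. This stands, and the point is therefore conditional. Weekly widening is not essential, though, since a starting window taken from diary sleep was enough for 69% rejection.
2. Only sleep-restriction deviation and one stimulus-control item are scored against the window. This stands. Because the article does not fix the Aim 2 measure, neither the affected nor the unaffected measures can be assumed.
3. A reader might take the slope rejection rates as the false-positive rates of the planned Aim 2 tests. They are not. The 2A interaction is inflated much less, and the Sobel path is inflated only when the arms differ in adherence. Since the trial expects that difference, 2B is not protected.
4. Earlier sleep in treatment may be an effect of earlier adherence, so conditioning on it removes genuine effect. This stands. It rules out making the adjusted model the main one, and it rules out concluding that adherence merely marks response if significance is lost.

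It can also be said that 2A is worded as an association, that Aim 2 is secondary, and that an analysis plan not shown may add covariates. The first two limit the importance of the point. On the third, the article does state a regressor list, and it attaches causal wording to Aim 2 and 2B.

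**Conclusion.** The point holds in a conditional form. Weekly diary-based review of time in bed, a one-sided score against prescribed times, and models without earlier sleep or the window are all in the article. If the window follows earlier sleep, a significant within-arm slope in 2A, or a mediated path in 2B when the arms differ in adherence, does not by itself show that adherence improved sleep.

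Under assumed inputs and no true effect, the slope is falsely significant in roughly 40% to 98% of trials, and the 2A interaction in 5% to 37%. The Sobel path is limited by the power of the arm difference in adherence. The trial's actual bias is unknown: it depends on the titration practice and on the adherence measure chosen, and could be small if measures not scored against the window dominate. The primary aim is unaffected. The remedy is cheap and changes what Aim 2 can claim.

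**What to change.** Keep the stated 2A and 2B models and add baseline diary sleep efficiency (weeks 1–2) as a covariate. It is measured before adherence is scored, so it carries no over-adjustment. Pre-specify three sensitivity analyses:

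- (a) The 2A regression and the adherence-to-sleep path of 2B, adding the time in bed prescribed for the week in which adherence is scored and mean sleep efficiency over the preceding treatment weeks.
- (b) A lagged model of sleep efficiency in week t+1 on adherence in week t, adjusting for sleep efficiency in week t and earlier and for prescribed time in bed in week t.
- (c) The same tests using the measures not scored against the window: the clinician-rated form and the share of wake minutes spent out of bed.

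State that the adjusted estimates are conservative because earlier sleep may itself result from earlier adherence, so loss of significance does not prove that adherence has no effect. Describe Aim 2 results as associations unless the unadjusted, adjusted and lagged results agree.

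Cost: no new data, since the diaries and the prescribed times needed for scoring are already held. There is extra analysis work, wider intervals, and partial over-adjustment in the sensitivity models. No treatment procedure changes.

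### Hypothesis 2A sets same-week adherence against diary sleep efficiency; if adherence is the diary score, shared waking minutes in bed can create a positive within-group slope with no effect on sleep

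*Protocol article*

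**What the plan says.** Protocol article, Statistical tests of hypotheses, Aim 2: the regression for 2A has "explanatory variables of group (dummy coded), adherence (in the last week of treatment), and group × adherence interaction". On the other side of the equation, "The outcome variable will be diary-derived sleep efficiency in the last week of treatment". The section adds "The interaction term is the effect of interest" and "Follow-ups will examine the adherence effect within each group". It does not name the adherence measure, and it lists no baseline sleep efficiency term.

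Sleep diaries: "Adherence to sleep restriction is calculated as average nightly deviation, in minutes, between the prescribed bed/wake times and reported times, plus any nap time". Going to bed later or rising earlier than scheduled is not counted against the client, so apart from naps only extra time in bed scores as non-adherence. Stimulus control has two items: the share of wake minutes spent out of bed, and "how many minutes outside the sleep window were spent in bed doing any activity other than sleep". PA-SMT has its own adherence measure, but the section says that the sleep restriction and stimulus control scores are calculated in that arm too.

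Limitations: the post-treatment "sleep diary and actigraphy data are collected between weeks 6–7 of treatment". Client adherence form: a clinician rating from 1 to 6 is a further adherence measure.

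Hypothesis 2B is tested by Sobel mediation through end-of-treatment adherence, with diary sleep efficiency at post-treatment and at 6 months as outcomes.

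**The concern.** Predictor and outcome belong to the same week and, if the diary score is used, to the same diary nights. Minutes awake in bed outside the window lower the adherence score and lower sleep efficiency at once, whatever happens to sleep itself. A positive slope in a CBTI arm could then be read as evidence that adherence improves sleep when it partly restates how efficiency is calculated.

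Aim 2 is meant to show whether adherence is directly related to outcome, and one of the two main planned publications rests on it. The post-treatment mediation in 2B uses the same pair of variables for its mediator-to-outcome path, so it is exposed in the same way.

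**Working it through.** **The plan's own figures.** The article gives no operating characteristic for 2A. Its only power figure, 0.81, belongs to Hypothesis 1A and has no bearing here.

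**Inputs.** From the article: 40 clients per arm; alpha 0.05 two-tailed (stated for 1A, adopted here); the timing and score definitions above. Assumed: sleep efficiency is total sleep time over time in bed (no formula is given); window W with mean 400 min (SD 40); efficiency inside the window s with mean 86% (SD 7), independent of adherence; excess minutes in bed E gamma-distributed with mean 10 to 50; a fraction φ giving the rate of sleep in the extra minutes relative to that inside the window.

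**Formula.** The adherence score is −E, and

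SE = 100 × s(W + φE) / (W + E).

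With φ = 1 this reduces to 100 × s, so there is no link with E. With φ = 0 it is 100 × sW / (W + E), which falls as E rises.

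**One client.** 345 min asleep in a 400-min window: 345/400 = 86.2%. With 30 waking minutes in bed outside the window: 345/430 = 80.2%. With 60: 345/460 = 75.0%. Sleep is the same in all three.

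**Simulation, 2,000 runs, no effect of adherence on sleep.** The nominal rate is 2.5% for a significant positive slope and 5% for the interaction. For the interaction test, adherence was standardised within arm.

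| Mean excess (min) | 10 | 20 | 35 | 50 |
|---|---|---|---|---|
| Correlation, none slept | 0.23 | 0.42 | 0.60 | 0.71 |
| Positive slope in one arm, none slept | 31% | 78% | 99% | 100% |
| Same, half slept (φ = 0.5) | 12% | 28% | 57% | 83% |
| Same, slept at the usual rate (φ = 1) | 3% | 3% | 3% | 2% |
| Interaction, PA-SMT on an unrelated own score, none slept | 17% | 52% | 87% | 97% |
| Same, half slept | 7% | 15% | 33% | 53% |
| Interaction, one diary score in all arms, none slept | 5% | 7% | 10% | 13% |
| Same, half slept | 4% | 5% | 6% | 5% |

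A second set of assumptions drew sleep time independently of time in bed (window 390–420 min, sleep SD 40–60 min, mean deviation 30–45 min; 1,000 runs per setting). The interaction was significant in about 3–4% of runs with a common score and in 28–82% with an unrelated PA-SMT score. With the common score, PA-SMT itself showed a significant positive slope in 58–98%.

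**Other adherence items.** The out-of-bed share of wake minutes correlates 0.59 with sleep efficiency if out-of-bed minutes are subtracted from time in bed, and 0.00 if they are not. A 1-to-6 rating unrelated to the diary minutes gives a significant positive slope in 2.5% of runs, the nominal rate.

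**Hypothesis 2B.** At post-treatment, mediator and outcome are the same pair as in 2A. At 6 months the outcome comes from a separate, later diary, so no minutes are shared.

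**The case against.** A reader might infer that 2A would be confirmed by construction. The article does not support that, for four reasons.

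- **The measure is not named.** The clinician rating is also an adherence measure and is not computed from diary minutes. This stands, with limits. The article's reason for not measuring adherence at follow-up, that no sleep schedules are prescribed then, fits the diary score better. The latent variable planned for 1A would also contain diary items. The rating comes from unblinded therapists after sessions in which diaries are reviewed, so it need not be independent of them.
- **The link is not inevitable.** If the extra time is slept at the usual rate, it vanishes. This stands for the sleep restriction deviation. It does not help the second stimulus control item, which counts only time not asleep, provided that time in bed includes those minutes. Naps matter only if they enter sleep efficiency.
- **The declared test is the interaction.** A link common to all arms largely cancels there, and a positive slope in PA-SMT would speak against the hypothesis. This stands if one score is used throughout. That the link exists only in the CBTI arms cannot be asserted, because the sleep restriction and stimulus control scores are also calculated in PA-SMT. Which score enters the model for that arm is left open.
- **Aim 2 is secondary and the trial is powered for 1A.** This stands and limits the severity.

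**Conclusion.** The point holds in a conditional form. The article fixes predictor and outcome to the same week, and its diary adherence scores share minutes with the sleep efficiency denominator. Under the assumptions listed, the planned within-group slopes can be significantly positive far more often than 2.5% with no benefit to sleep: 31–100% if none of the extra time is slept, 12–83% if half is, nominal if it is slept at the usual rate.

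The interaction is seriously at risk only if PA-SMT is scored on its own measure (17–97% with none slept); with one common score it is about 3–13%. The post-treatment part of 2B is exposed. It would go too far to extend this to the 6-month mediation. The primary analysis is not affected. This should be fixed, but it does not invalidate the trial.

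**What to change.** In Statistical tests of hypotheses, Aim 2:

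1. Name the adherence measure for 2A, and use one score defined alike in all arms compared. If it is the deviation from prescribed times, state which reference times apply in PA-SMT.
2. Use adherence averaged over sessions 3–6 as the predictor in 2A and as the mediator for post-treatment 2B, so that it precedes the outcome week.
3. Adjust for diary sleep efficiency from weeks 1–2.
4. A lag reduces the shared-minutes link but does not remove it when adherence is stable from week to week. So repeat 2A with post-treatment ISI adjusted for pre-treatment ISI, and claim that adherence drives outcome only if both analyses agree.

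Diary sleep efficiency stays the named outcome of 2A; replacing it would rewrite the hypothesis.

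Cost: wording and slightly more analysis, since all the data are already collected. The lagged predictor will probably show a somewhat weaker association.
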